**Quality: Low-Value Care**

| Measure                                         | Source                                                    | Day(s) Obtained |
|-------------------------------------------------|-----------------------------------------------------------|-----------------|
| Use of inappropriate medications in the elderly | RA via EHR/MAR                                            | Daily           |
| Use of foley catheter                           | RA via MD/RN for home patients; EHR review for inpatients | Daily           |
| Use of restraints                               | RA via MD/RN for home patients; EHR review for inpatients | Daily           |

**Patient Functional Status and Quality of Life**

| Measure        | Source         | Day(s) Obtained                |
|----------------|----------------|--------------------------------|
| EuroQol -5D-5L | RA via patient | Admission, discharge, +30      |
| SF-1           | RA via patient | -30, admission, discharge, +30 |

|                                                                                                     |                |                                |
|-----------------------------------------------------------------------------------------------------|----------------|--------------------------------|
| Activities of daily living: admission to discharge; admission to 30-day post-discharge              | RA via patient | -30, admission, discharge, +30 |
| Instrumental activities of daily living: admission to discharge; admission to 30-day post-discharge | RA via patient | -30, admission, discharge, +30 |
| Patient Health Questionnaire-2                                                                      | RA via patient | Admission, discharge, +30      |
| PROMIS Emotional Support Short Form 4a                                                              | RA via patient | Admission, discharge, +30      |
| Days at home since discharge                                                                        | RA via patient | +30                            |
| Milestones                                                                                   |                |                                |
| Walk around ward/home                                                                               | RA via RN      | Discharge                      |
| Get to (non-commode) bathroom                                                                       | RA via RN      | Discharge                      |
| Walk 1 flight of stairs                                                                             | RA via RN      | Discharge                      |
| Visit with friends/family                                                                           | RA via patient | Discharge                      |
| Walk outside around my home                                                                         | RA via patient | +30                            |
| Go shopping                                                                                         | RA via patient | +30                            |
| Post-Hospital Syndrome measures                                                                     | RA via patient | Admission, +3, +30             |

### Patient and Family Experience

| Measure                         | Source         | Day(s) Obtained |
|---------------------------------|----------------|-----------------|
| 3-item Care Transition Measure  | RA via patient | +30             |
| Picker Experience Questionnaire | RA via patient | +30             |
| Global satisfaction             | RA via patient | +30             |
| Qualitative interviews          | See Below      | +30             |

### Process Measures

| Measure                                              | Source            | Day(s) Obtained |
|------------------------------------------------------|-------------------|-----------------|
| Time from admission decision to assessment by RA     | RA                | Admission       |
| Time from RA assessment to dismissal                 | RA                | Admission       |
| Time from arrival home or to floor and MD evaluation | RA via MD         | Admission       |
| Time from arrival home or to floor and RN evaluation | RA via RN         | Admission       |
| RN to patient ratio                                  | RA via census     | Daily           |
| Number of RN visits                                  | RA via RN/EHR     | Daily           |
| Number of “on call” MD interactions (video or phone) | RA via MD         | Daily           |
| Number of “on call” MD in-person visits              | RA via MD         | Daily           |
| Duration of 1 st RN visit                 | RA via RN         | Daily           |
| Duration of subsequent RN visit                      | RA via RN         | Daily           |
| Clinician focus group                                | All clinicians    | Post-study      |
| Failed stethoscope transmissions, number and %       | RA via clinicians | Daily           |

### Artificial Intelligence Measures

| Measure                                                                                                                                                             | Source             | Day(s) Obtained |
|---------------------------------------------------------------------------------------------------------------------------------------------------------------------|--------------------|-----------------|
| Specificity                                                                                                                                                         |                    |                 |
| Sensitivity                                                                                                                                                         |                    |                 |
| Positive predictive value                                                                                                                                           |                    |                 |
| Negative predictive value                                                                                                                                           |                    |                 |
| Accuracy of categorization by emergent, significant, and borderline, and normal (as outlined by Smith et al)                                           |                    |                 |
| ECGs with no undercalls and no overcalls, stratified by all, with $\geq 1$ abnormality, $\geq 1$ major abnormality, $\geq 1$ emergency (as outlined by Smith et al) |                    |                 |
| Timed Walking                                                                                                                                                       | RA                 | Daily           |
| Timed Stairs                                                                                                                                                        | RA                 | Daily           |
| Gait                                                                                                                                                                | RA                 | Daily           |
| Use of Assistive Device                                                                                                                                             | RA                 | Daily           |
| Balance Questions to assess Fall risk                                                                                                                               | Patient            | Daily           |
| Timed Up and Go Balance Test                                                                                                                                        | RA                 | Daily           |
| 30 Second Chair Stand Test                                                                                                                                          | RA                 | Daily           |
| 4 Stage Balance Test                                                                                                                                                | RA                 | Daily           |
| Loss of Consciousness in the past 24 hours                                                                                                                          | Patient            | Daily           |
| Cough and Inducible Cough                                                                                                                                           | RA                 | As needed       |
| Respiratory Rate                                                                                                                                                    | RA                 | 3-6x Daily      |
| Inspiratory to Expiratory Ratio                                                                                                                                     | RA                 | 1-2x Daily      |
| Orthostatic Vitals                                                                                                                                                  | RA                 | 1-2x Daily      |
| Lab Values via capillary stick (used only for research)                                                                                                             | RA                 | 1-2x Daily      |
| Acoustic Respiratory Rate                                                                                                                                           | RA                 | Daily           |
| Number of times patient got up during the night (to urinate)                                                                                                        | Patient            | Daily           |
| Richards-Campbell Sleep Questionnaire                                                                                                                               | Patient            | Daily           |
| STOP-Bang Questionnaire                                                                                                                                             | Patient            | On admission    |
| 10 Question Perceived Stress Questionnaire                                                                                                                          | Patient            | Daily           |
| Live Telemetry Alarms                                                                                                                                               | Doctor, Nurse, EMT | As they occur   |

For electrocardiographic categorizations, see Smith et al

For nonelectrocardiographic categorizations, see Appendix

#### Covariates of Interest

| Measure                                      | Source                  | Day(s) Obtained |
|----------------------------------------------|-------------------------|-----------------|
| Age                                          | RA via EHR a | Admission       |
| Gender                                       | RA via EHR              | Admission       |
| Race/ethnicity                               | RA via patient          | Admission       |
| Primary language                             | RA via EHR              | Admission       |
| Health insurance status, public/private/none | RA via EHR              | Admission       |
| BMI                                          | RA via EHR              | Admission       |

|                                                               |                         |                |
|---------------------------------------------------------------|-------------------------|----------------|
| Comorbidities, type and #                                     | RA via EHR and H&P      | Admission      |
| Partner status                                                | RA via patient          | Admission      |
| Education                                                     | RA via patient          | Admission      |
| Zip code                                                      | RA via EHR              | Admission      |
| Employment                                                    | RA via H&P              | Admission      |
| Smoking status                                                | RA via H&P              | Admission      |
| Medications used as outpatient, #                             | RA via EHR              | Admission      |
| DNR/I code status                                             | RA via H&P              | Admission      |
| Home health aide prior to admission                           | RA via patient          | Admission      |
| Readmission risk score on discharge (HOSPITAL)                | RA via EHR              | Discharge      |
| Elective and urgent admissions in the previous year, #        | RA via EHR and patient  | Admission      |
| ED visits in the previous 6 months, #                         | RA via EHR and patient  | Admission      |
| Interqual disease-specific leveling                           | RN                      | Admission      |
| PRISMA-7                                                      | RA via patient          | Admission      |
| Eight-item Interview to Differentiate Aging and Dementia      | RA via patient or proxy | Admission      |
| Would you be surprised if this patient died in the next year? | RA via MD               | Admission      |
| BRIEF health literacy screening tool                          | RA via patient          | Admission      |
| Caregiver burden                                              | RA via caregiver        | Admission, +30 |
| Lives alone                                                   | RA via patient          | Admission      |

a: Note that RA will recheck covariates after MD H&P completed to ensure comorbidities and other covariates correctly captured

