## SUBJECT SELECTION

### Inclusion/exclusion criteria

#### *Inclusion*

- Social
  - Resides within either a 7.5-mile driving radius of the BWFH emergency room
    - Driving radius will be obtained via inputting a nearby (but not exact) address into Google Maps.
  - Has capacity to consent to study OR can assent to study and has proxy who can consent (see subject enrollment, below)
  - Can identify a potential caregiver who agrees to stay with patient for first 24 hours of admission. Caregiver must be competent to call care team if a problem is evident to her/him. After 24 hours, this caregiver should be available for as-needed spot checks on the patient.
    - This criterion may be waived for highly competent patients at the patient and clinician's discretion.
- Clinical
  - $\geq 18$  years old
  - Primary or possible diagnosis of cellulitis, heart failure, complicated urinary tract infection, pneumonia, COPD/asthma, other infection, chronic kidney disease, malignant pain, diabetes and its complications, gout flare, hypertensive urgency, previously diagnosed atrial fibrillation with rapid ventricular response, anticoagulation needs, or a patient who desires only medical management that requires inpatient admission, as determined by the emergency room team.
    - Regarding anticoagulation needs, this includes a patient who requires therapeutic anticoagulation and concomitant monitoring (thus requiring inpatient status)
    - Regarding a patient who desires only medical management, this includes a patient who requires acute care for symptom management, but declines any surgical intervention. This may include a patient who is about to transition to hospice care, for example, but still has the functional capacity to meet our criteria below. Under these circumstances, we would make sure that various contingencies, including possible transition to hospice care or hospital readmission, are completely understood by patients and caregivers as applicable.
    - In order to achieve enrollment goals, we *a priori* reserve the ability to expand this criterion to include patients who fail observation status and patients who

are transferred to the observation unit under the care of the emergency room observation team.

- Regarding IBD
  - Requires intravenous infusion and acute care monitoring per outpatient gastroenterologist
- Regarding acute pancreatitis
  - Please refer to attachment

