## Statistical methods

### *Home hospital vs traditional hospital*

#### *Quantitative*

We plan to form 3 different control groups (with groups listed in order of preference):

1. Patients who were deemed eligible for home hospital, but the service was full (and they were not enrolled subsequently if the service was no longer full);
2. Patients who were deemed eligible for home hospital, but lived outside of the 7.5-mile catchment area; and
3. Patients who were admitted to the hospital.

For each control group, we will use propensity score weighting, adjusting for covariates of interest (see table above), baseline functional status, and DRG. We will be cognizant of over-adjustment depending on our final sample size for each group above. If possible, we will use only group 1 above, as it is the strongest. If we have insufficient control group sample size, we may choose to combine groups 1 and 2 above.

The primary outcome (hospitalization cost) will be assessed using a generalized linear model assuming a gamma distribution with a log link. We will use a multivariable regression approach for secondary

outcomes, using logistic regression for binary outcomes and non-transformed linear regression for normally distributed continuous outcomes as appropriate.

We *a priori* plan to perform a subgroup analysis that does not involve any outlier participants, should this occur. We also *a priori* plan subgroup analyses by diagnosis, by age group, by disposition, by location of admission (e.g., ED, floor, clinic, and home), and by daily activity level. We also *a priori* plan to analyze our outcomes with means, but also with median and interquartile ranges, which are less subject to outlier effects. We may choose to employ non-parametric tests of significance should our data be nonparametric.

We *a priori* plan to adjust our secondary analyses using the Benjamini-Hochberg method. We *a priori* choose a false-discovery rate of 0.20.

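### Caregiver burden at 30 days after discharge is listed only as a covariate, and the propensity-weighting rule does not keep this post-treatment value out of the weights

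*Protocol*

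**What the plan says.** In the protocol's Covariates of Interest table, "Caregiver burden" is a row with source "RA via caregiver", obtained at admission and at +30 days. It appears in no other table, and the aims, the Study endpoints table and the Summarizing Adverse Events list do not mention it. In the table headed "Patient and Family Experience", the three scored instruments are all taken from the patient. The fourth row, qualitative interviews, refers to a later section under which a sample of caregivers is interviewed as well.

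For home versus traditional hospital, Statistical methods states: "For each control group, we will use propensity score weighting, adjusting for covariates of interest (see table above), baseline functional status, and DRG". It adds: "We will be cognizant of over-adjustment depending on our final sample size for each group above". The sections on early transfer and on the paramedic comparison both say that they use the same analysis.

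On the caregiver's role, the social inclusion criteria read "Can identify a potential caregiver who agrees to stay with patient for first 24 hours of admission", with availability for spot checks afterwards. They also provide that "This criterion may be waived for highly competent patients".

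**The concern.** Propensity weighting is meant to balance the groups on what preceded treatment. A value taken 30 days after discharge cannot have influenced who went home. It may well be a result of going home, because the home model asks a caregiver to stay for the first day and remain on call. Balancing on it means balancing on a possible consequence of treatment.

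Two things are at stake. First, the weighted cost contrast may be biased, and cost is the primary endpoint both for home versus traditional hospital and for early transfer. Second, the 30-day burden score, which is the natural quantitative measure of load passed to families, is collected but has no stated analysis as an outcome.

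**Working it through.** No figure in the protocol bears on this point, so there is none to reproduce. The check sets the relevant sections side by side.

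1. **Timing within the table.** Covariates of Interest has 25 rows. One (the HOSPITAL readmission score) is obtained at discharge, and one (caregiver burden) at admission and +30. The other 25 − 2 = 23 are obtained at admission only. The table is therefore not confined to baseline values, and caregiver burden is its only row with a post-discharge value.

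2. **How the table enters the weights.** The weighting sentence cites the table as a whole. The word baseline qualifies only functional status, whose measures are likewise collected at several times, up to +30. So where a measure outside the table has several time points, the sentence names the one to use. For the table itself it does not.

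3. **Whether another sentence excludes the +30 value.** The over-adjustment caveat depends on the final sample size, not on when a variable is measured. It could shorten the covariate list but gives no rule against post-treatment values.

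4. **Which comparisons are exposed.**
   - Home versus traditional hospital: weighted; primary endpoint is cost of the acute episode.
   - Early transfer: same method; primary endpoint is cost of the episode plus 30 days.
   - Paramedic: same method, but both groups are cared for at home, so the demand on the caregiver at home does not separate them.
   - Remote versus in-person: randomized and not weighted. The named adjustment set omits caregiver burden, and covariates may be added only for differences at baseline, which a +30 value cannot show.

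5. **Direction of a possible bias.** Write burden at +30 as B = c·U + d·H + noise, where U is severity of the illness course, H is 1 for home care and 0 otherwise, and c and d are constants. If c > 0 and d > 0, then at equal B the home patients have lower U on average. When U also raises cost, weighting on B makes home care look cheaper than it is. If d < 0 the direction reverses. If d = 0 this mechanism produces no bias. The protocol gives no value for c, for d or for the effect of U on cost. It also does not say how much of U the other covariates, functional status and DRG would already capture. The size therefore cannot be derived.

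6. **Definedness.** Because the caregiver criterion can be waived, some patients may have no burden value at either time. The weighting rule does not say how they are handled.

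**The case against.** The strongest reply is that the protocol never says which of the two burden values enters the model. The admission value is a legitimate covariate, and a sensible analyst would use it. Final covariate choice is often settled in a statistical analysis plan, which is not at hand. This stands in part: use of the +30 value is permitted by the wording, not announced. But the protocol does name the covariate set, and the set as named includes a post-discharge measurement. The point is about what is written, not about missing detail.

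A second reply is practical. Controls are patients who were not enrolled, the evaluation is described as retrospective, and no procedure is given for reaching their caregivers at +30. Without that value in controls, it could not serve as a weighting variable. This stands too. It lowers the chance that the error is carried out, and it means that a home-versus-hospital comparison of burden may not be possible with the data planned.

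Third, the Study endpoints table lists only headline endpoints. Many collected outcomes, such as the EuroQol and activities of daily living, are not in it either. Absence from that table alone shows little. The difference is that those measures sit in outcome tables, while caregiver burden is filed only under covariates.

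Some stronger readings are tempting but unsupported. A reader might infer that burden on families goes unmeasured. It does not: the +30 value is collected, and a sample of caregivers is interviewed, although the interviews are qualitative. A reader might also infer bias in the adverse-event contrasts. Adverse events are the primary endpoint only in the remote versus in-person and paramedic comparisons. The first uses no weighting, and in both the caregiver-load mechanism does not distinguish the groups.

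**Conclusion.** The point holds as a specification error in the non-randomized analyses, chiefly home versus traditional hospital and early transfer. The protocol's rule admits a post-treatment value into the propensity weights, and no other sentence excludes it. Harm to the cost contrast requires that the +30 value is actually used, that it was obtained in both groups, that home care changes burden, and that burden tracks an illness course related to cost. Under those conditions, with burden raised by home care, the bias would favour home care. Its size is not fixed by anything in the documents, and no percentage should be attached to it.

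For the randomized comparison there is no weighting problem. What remains there is only that a collected measure relevant to families is not listed as an outcome.

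**What to change.** - In Statistical methods, home versus traditional hospital, state that only admission values from the Covariates of Interest table enter the propensity and outcome models. For caregiver burden, use the admission value with a no-caregiver category. The early transfer and paramedic analyses inherit the change.
- Move the +30 value to the Patient and Family Experience table as a secondary outcome, adjusted for the admission value. Analyse it in the remote versus in-person trial. Analyse it in home-versus-hospital comparisons only if it was obtained from caregivers in both groups.
- Note the side effect: the same sentence takes the HOSPITAL score, obtained at discharge, out of the propensity models. That score is also named in the randomized trial's adjustment set, where its timing should be looked at separately.

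The cost is a few sentences and one more outcome model. The randomized comparison needs no new data. The downside is an additional secondary outcome, defined only for patients with a caregiver.
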